[figure not shown]

## Study summary

The purpose of this work is to investigate the effect of various interventions i.e. lens replacement (during a lens wearing day) and lens manipulation on comfort in contact lens wear.

Up to 30 soft contact lens wearers will be recruited for this study. All volunteers will be symptomatic (i.e. classified as symptomatic according to method of Young et al.). Subjects will attend the clinic for six visits over four days. Subjects will wear their habitual contact lenses during the course of this investigation. Various interventions i.e. lens replacement and lens manipulation [i.e. the contact lens is slid off the cornea onto the temporal sclera and then repositioned (this is known as the 'scleral swish')] will be performed in order to assess their impact on lens discomfort. Comfort scores will be collected at different times of the day mainly via SMS (text) messaging.

A study summary is shown in Table 1.

| Visit |                            | Procedures                                                                                                                                                                                                                                                                                         |
|-------|----------------------------|----------------------------------------------------------------------------------------------------------------------------------------------------------------------------------------------------------------------------------------------------------------------------------------------------|
| Day 1 | Visit 1                    | Explanation of study procedures and visits
Confirmation that all inclusion/exclusion criteria are met
Information and consent forms and study summary signed
Ocular history
Ocular symptoms measurement
Visual acuity measurement
Lens fit assessment
Slit lamp biomicroscopy |
| Day 2 | Visit 2
(morning)       | Comfort score prior to lens application both eyes
Lens application
Comfort score after 6 minutes both eyes                                                                                                                                                                                   |
|       | Visit 3
(5 hours later) | Lens replacement or lens manipulation on each eye
Comfort scores after 6 minutes both eyes                                                                                                                                                                                                      |
| Day 3 | Visit 4
(morning)       | Comfort score prior to lens application both eyes
Lens application
Comfort score after 6 minutes both eyes                                                                                                                                                                                   |
|       | Visit 5
(5 hours later) | Lens replacement or lens manipulation on each eye
Comfort scores after 6 minutes both eyes                                                                                                                                                                                                      |
| Day 4 | Visit 6                    | Visual acuity measurement
Slit lamp biomicroscopy
Exit form completed                                                                                                                                                                                                                        |

**Table 1: Study summary.**

## Section 1. Overview

### 1.1 Background

Discomfort with soft contact lenses remains a major issue for the industry, giving rise to millions of discontinuing wearers each year. Indeed, the key reason to discontinuation from lens wear is some form of discomfort. Despite the obvious commercial benefits of better knowledge in this area, a comprehensive understanding of the determinants of contact lens comfort remains elusive. Over the past 20 years, various investigators have sought to relate factors such as lens design (e.g. nature of the lens edge, dehydration, and tear film thickness/stability to contact lens comfort; however, such factors do not appear to fully explain the nature of contact lens comfort.

Frequency of lens replacement may influence comfort in contact lens wear. Several studies have shown that when contact lenses are replaced more frequently, comfort ratings increase. Symptoms of discomfort in contact lens wear may increase towards the end of the day. Assessing the effect of replacing contact lenses during a lens wearing day may allow further insight into what factors (i.e. ocular factors or contact lens factors) mediate end of day discomfort.

The purpose of this work is to investigate the effect of various interventions i.e. lens replacement and manipulation during a lens wearing day on the comfort of a group of symptomatic contact lens wearers. Subjects will wear their habitual contact lenses during the course of the study. Various interventions i.e. lens replacement and lens manipulation ('scleral swish') will be performed in order to assess their impact on lens discomfort. On two separate days four interventions (chosen randomly) will be performed. All volunteers will be symptomatic (i.e. classified as symptomatic according to method of Young et al.). We will collect contact lens comfort scores at different times of the day mainly via SMS (text) messaging.

### **1.3 Study objectives**

This study seeks to investigate the effect of various interventions i.e. lens replacement and manipulation during a lens wearing day on comfort in contact lens wear.

### **1.4 Study design**

This clinical study will be a randomised and subject-masked (interventions and comfort scores) study which will take place at a single study site. Up to 30 soft contact lens wearers will be recruited. Subjects will wear their habitual contact lenses during the course of this investigation. Various interventions i.e. lens replacement and manipulation will be performed in order to assess their impact on lens discomfort. Comfort scores will be collected at different times of the day mainly via SMS (text) messaging.

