**2.6.1 Lenses**

Subjects will use their own daily disposable contact lenses. A description of the various interventions to be investigated in this study are shown in Table 2.

| Interventions  | Description                                                                                                   |
|----------------|---------------------------------------------------------------------------------------------------------------|
| Intervention 1 | No intervention                                                                                               |
| Intervention 2 | The contact lens will be removed and replaced by a fresh contact lens.                                        |
| Intervention 3 | The contact lens will be removed and replaced by the same contact lens.                                       |
| Intervention 4 | The contact lens will be slid off the cornea onto the temporal sclera and then repositioned ('scleral swish') |

Table 2: Description of interventions

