### **3.2.1.2 Day 2**

#### **3.2.1.2.1 Visit 2**

Subjects will attend the clinic in the morning. They will be asked to attend the clinic without lenses in situ, but to bring their lenses with them. Comfort scores will be recorded (on paper) prior to lens application. Contact lenses will be applied and comfort scores will be collected after 6 minutes via SMS. Subjects will wear their contact lenses for at least 12 hours and will provide comfort scores at various times of the day (Table 4) via SMS messaging using the same rating scale. Subjects will be asked to return 5 hours after lens application.

| Time of the day                  | Comfort measurement |
|----------------------------------|---------------------|
| Prior to lens application        | Paper               |
| 6 minutes after lens application | SMS                 |
| 1 hour after lens application    | SMS                 |
| 2 hours after lens application   | SMS                 |
| 3 hours after lens application   | SMS                 |
| 4 hours after lens application   | SMS                 |
| 5 hours after lens application   | Paper               |
| 6 min after intervention         | Paper               |
| 6 hours after lens application   | SMS                 |
| 7 hours after lens application   | SMS                 |
| 8 hours after lens application   | SMS                 |
| 9 hours after lens application   | SMS                 |
| 10 hours after lens application  | SMS                 |
| 11 hours after lens application  | SMS                 |
| 12 hours after lens application  | SMS                 |
| Every hour until lens removal    | SMS                 |

Table 4: Times of comfort measurement

### 3.2.1.2.2 Visit 3

Subjects will return to the clinic 5 hours after lens application. The investigator will perform the intervention randomly assigned to each eye (Appendix C). The investigator will make every effort to keep the intervention masked from the subject. Comfort scores will be recorded on paper prior to the intervention and 6 minutes after the intervention. Subjects will then be asked to continue wearing their lenses and to provide comfort scores via SMS (Table 4) until they remove their lenses.

Subjects will be asked to attend the next scheduled visit (Study Day 2).

### 3.2.1.3 Day 3

#### 3.2.1.3.1 Visit 4

The same procedures as at the Study Visit 1 will be carried out.

#### 3.2.1.3.2 Visit 5

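### Section 1.4 claims subject masking to all interventions, but only fresh versus same lens can plausibly be masked, because Intervention 1 leaves the eye untouched beside a handled fellow eye

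*Protocol*

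**What the plan says.** Section 1.4 calls this a "randomised and subject-masked (interventions and comfort scores) study", without limiting the claim to any pair of interventions.

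Table 2 in section 2.6.1 defines four conditions. The first is "No intervention", so that eye is left alone. The second and third both take the lens out of the eye; they differ only in whether a new lens or the worn one then goes in. The fourth is a manipulation without removal: "The contact lens will be slid off the cornea onto the temporal sclera and then repositioned".

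Section 3.2.1.2.2 (Visit 3) covers delivery: "The investigator will perform the intervention randomly assigned to each eye". On masking it adds only this: "The investigator will make every effort to keep the intervention masked from the subject". Comfort is rated by the subject just before the intervention, 6 minutes after it, and then hourly (Table 4). Section 1.5 states the principal hypothesis as equivalence of comfort across all the interventions, so Intervention 1 is included. The only bias control named in section 2.7 is random order.

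**The concern.** A subject who is awake can tell an eye that was left alone from one whose lens was taken out or slid aside, and can probably tell a slide from a removal. The protocol therefore claims a property that the design, as described, does not have for most of its contrasts.

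This matters because the outcome is entirely the subject's own rating. If symptomatic wearers expect a handled eye to feel better, or worse, that expectation enters the score, and no analysis can later separate it from the effect of the intervention. A report that repeats the wording of 1.4 would claim masking for comparisons that lacked it. Since the gap lies in how the interventions are delivered, a statistical analysis plan could not close it.

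**Working it through.** The protocol gives no figure on this point to reproduce. The check sets the sections side by side and counts allocations and contrasts.

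**1. Is the untouched eye always beside a handled one?** Inputs:

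- Section 1.1: four interventions over two separate days.
- Section 3.2.1.2.2: one intervention assigned to each eye at the 5-hour visit.
- Section 3.2.1.3.2: the second day's interventions differ from the first day's. That section refers to Study Visit 2. I read this as the Day 2 intervention visit, which Table 1 numbers Visit 3.

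Two eyes on two days give 2 × 2 = 4 eye-days for four interventions. If each is used once, there are 4! = 24 allocations. Intervention 1 can take any of 4 eye-days. The fellow eye that day then receives 2, 3 or 4, and the remaining two interventions can be ordered in 2! = 2 ways. Each fellow-eye intervention therefore occurs in 4 × 2 = 8 allocations, and 8 + 8 + 8 = 24. In 24 of 24 allocations the subject has one untouched and one handled eye at the same visit.

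**2. Which contrasts can be masked?** Four interventions give 4 × 3 / 2 = 6 pairwise contrasts.

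| Contrast | What the subject experiences | Masking as described |
|---|---|---|
| 1 v 2, 1 v 3, 1 v 4 | untouched v handled | not possible |
| 2 v 4, 3 v 4 | removal and re-insertion v slide | doubtful |
| 2 v 3 | removal and re-insertion in both | plausible |

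Three contrasts are plainly unmasked, two probably are, and one remains.

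**3. Does other text restore masking?**

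- The commitment in 3.2.1.2.2 is to effort; it names no method.
- Random order (2.7) balances order and day. It does not act on expectation.
- Section 2.11 limits the specific information passed to participants, but it cannot hide whether an eye was handled.
- Even 2 v 3 needs a procedure. Under sections 2.6, 2.6.1 and 3.2.1.2.1 no lenses are issued and subjects bring their own, so visible use of a fresh lens from that supply could reveal the allocation.

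**4. A related inconsistency.** For Visits 3 and 5, Table 1 lists replacement or manipulation for each eye. That does not fit the row "Intervention 1 | No intervention" in Table 2.

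**The case against.** The strongest reply is that 3.2.1.2.2 promises only best effort, that a do-nothing control is a legitimate way to separate handling from the passage of time, and that the appendices on assignment and subject information are not available. All three points are fair. The do-nothing control need not change, and a concealment step could be set out in an appendix, although the body text refers to none. But a best-effort sentence in section 3 does not qualify the flat claim in 1.4, and effort cannot make an untouched eye feel handled.

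Four stronger readings are tempting, and the documents do not support them.

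- *A false-positive rate can be attached to the problem.* The protocol gives no standard deviation, no size of bias and no test. Nor does it clearly fix the scale of the hourly scores: 100-point scales are specified for symptoms at Visit 1, while Visit 2 mentions only the same rating scale. The stated hypothesis is also equivalence. A shift with no true effect would then mainly make equivalence harder to show, and a shift against a true effect could hide it.
- *Masking to comfort scores is impossible because the subject gives them.* The phrase may mean that earlier scores are not visible at the next rating. It is unclear rather than shown to be wrong.
- *Intervention 2 versus 3 must be named the key comparison.* Section 1.1 speaks of insight into ocular and lens factors but ranks no contrast, and ranking can be left to the analysis plan.
- *The untouched eye needs dummy handling.* Such handling may itself affect comfort and would change the control condition, so it is a trade-off and not a correction.

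**Conclusion.** The masking claim in 1.4 is too broad. As described, it can plausibly hold for one of six contrasts (2 versus 3), fails for the three with Intervention 1, and probably fails for the two of Intervention 4 with 2 or 3. Comfort ratings in those five contrasts are open to expectation bias of unknown size and direction.

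The fellow-eye result assumes that each intervention is used once per subject, which the body text implies but the unavailable randomisation table would have to confirm. The judgement that a slide can be told from a removal is a reasonable inference that the protocol does not state.

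A reader might go further and infer that the results will be biased or that the trial is invalid. The documents show a risk and an overstated claim, and no more than that. The change is still worth making because it governs what may be concluded from a wholly subjective outcome.

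**What to change.** 1. In 1.4 and 3.2.1.2.2, restrict the subject-masking claim to Intervention 2 versus 3. State that the lens, fresh or worn, is kept out of the subject's sight, including when a fresh lens is taken from the subject's own supply.
2. In the same places, state that contrasts with Intervention 1, and those of Intervention 4 with 2 or 3, are unmasked and will be interpreted as such.
3. In 1.4, say what masking to comfort scores means (for example, earlier scores not visible when rating) or delete it.
4. Reconcile the Table 1 entries for Visits 3 and 5 with the untouched condition in Table 2.

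The cost is protocol wording plus a simple routine for keeping lenses out of view. The price is a narrower masking claim. Interventions, visits and subject numbers stay as they are.

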### **1.5 Statistical considerations**

The principal hypotheses to be tested in this work is that ocular comfort scores will be substantially equivalent for all the interventions assessed.

Given the lack of previous data with which to conduct a priori calculations for subject numbers for the study, we decided to use up to 30 subjects as we think this number of subjects is sufficient for the project to be worthwhile.

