### **3.2 Visit conduct**

#### **3.2.1.1 Day 1: visit 1.**

The subject will receive a study-specific information form outlining the study at least 24 hours before the initial visit, and will be required to sign an informed consent form and a study summary form at this visit, prior to enrolment (Appendix C). Copies of the signed forms will be issued to the subject. When the subject has signed the consent form, they are considered to be enrolled on the study. Subjects should be asked to attend this visit with their lenses in situ and to bring their habitual care regimen with them.

The following procedures will be performed:

1. Details of the ocular history.
2. The investigator will confirm that the subject satisfies all the inclusion and exclusion criteria. Subjects who fail to meet all the criteria at this time will be discontinued and replaced.
3. High contrast logMAR visual acuity in accordance with the current Eurolens Research Standard Operating Procedure 'Assessment of visual performance using the Bailey-Lovie logMAR visual acuity test chart and procedures for carrying out an over-refraction'.

4. Ocular symptoms will be measured using Contact Lens Dry Eye Questionnaire - 8 (CLDEQ-8) and 100-point vertical visual analogue scales (Appendix C).
5. Lens fit will be assessed using the following evaluations: horizontal and vertical centration, corneal coverage and movement. Normally, for an acceptable fit, centration and movement will fall within currently accepted clinical criteria [between -1 and +1 on a -2 to +2 grading scale (Appendix C)]. Lens deposition and wettability will also be graded using the grading scales in Appendix C.
6. Slit lamp biomicroscopy will be carried out for the signs outlined in Table 2 and in accordance with the current Eurolens Research Standard Operating Procedure 'Examination of the anterior segment using slit lamp biomicroscopy'. Grades will be scored to the nearest 0.1 in the best judgement of the investigator using Efron Grading Scales.

| Classification | Primary signs                                                                                                                                                                                                    | Secondary signs                                                                                                                                                                |

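### The principal hypothesis claims equivalence of all interventions but has no margin, so it cannot be tested as worded and does not match the stated objective

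*Protocol*

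**What the plan says.** Protocol section 1.5 gives one principal hypothesis to be tested: "ocular comfort scores will be substantially equivalent for all the interventions assessed". Section 2.6.1 (Table 2) lists four interventions, one of which is no intervention. Nothing in the protocol says how close scores must be to count as equivalent: there is no margin in comfort points and no confidence-interval criterion.

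Section 1.3 puts the aim differently: "This study seeks to investigate the effect of various interventions" on comfort. Section 1.4 likewise says the interventions are done to assess their impact on discomfort.

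On numbers, section 1.5 begins "Given the lack of previous data with which to conduct a priori calculations for subject numbers for the study" and continues "we decided to use up to 30 subjects as we think this number of subjects is sufficient for the project to be worthwhile". No significance level, power, SD or effect size is stated.

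On design, section 1.1 says "On two separate days four interventions (chosen randomly) will be performed", and the Visit 3 procedures (3.2.1.2.2) say "The investigator will perform the intervention randomly assigned to each eye". Two eyes on two days give four eye-days per subject, so the comparisons are within subject.

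**The concern.** Equivalence can be tested only against a margin, because the margin is part of the hypothesis. Without one, the only test available is a test of difference. A non-significant result from that test could then be taken to support the principal hypothesis, and a small or noisy study would produce that result most easily.

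What the trial may conclude is at stake. Section 1.1 hopes that replacing lenses during the day will show whether ocular or lens factors drive end-of-day discomfort. Because one condition is no intervention, equivalence of all four would mean that neither a fresh lens nor manipulation changes comfort. A null result from up to 30 subjects may be too weak to carry that conclusion.

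**Working it through.** There is no sample-size calculation to reproduce, so the check asks what 30 subjects can show.

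**Inputs.** From the protocol: n = 30 (the ceiling in 1.5), four interventions, hence 4 × 3 / 2 = 6 pairs, compared within subject. Assumed: two-sided 5% for difference tests, 5% for each one-sided equivalence test, one score per intervention, all 30 complete, and the same SD of the paired difference for every pair (exchangeable conditions). Effects d and margins are in units of that SD.

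**1. One pair, paired t-test.** Power comes from the noncentral t distribution with 29 df, noncentrality d√30 and critical value 2.045 (unadjusted).

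| True d | d√30 | Power | Non-significant | Non-significant, Bonferroni for 6 pairs |
|---|---|---|---|---|
| 0.3 | 1.64 | 0.355 | 64% | 86% |
| 0.4 | 2.19 | 0.563 | 44% | 72% |
| 0.5 | 2.74 | 0.754 | 25% | 53% |

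Power reaches 80% at d = 0.53. With 20 completers, d = 0.5 is missed 44% of the time (power 0.565).

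**2. Omnibus repeated-measures F test, one intervention differing from the other three by d.** The residual variance is half the variance of the paired difference, and the squared deviations of the four means sum to 0.75d². The noncentrality is therefore 30 × 0.75d² × 2 = 45d², with 3 and 87 df and critical value 2.709.

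| d | Noncentrality | Power | Missed |
|---|---|---|---|
| 0.3 | 4.05 | 0.348 | 65% |
| 0.4 | 7.20 | 0.582 | 42% |
| 0.5 | 11.25 | 0.794 | 21% |

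**3. Formal equivalence, true difference zero.** Equivalence is declared for a pair if its 90% CI, mean ± 1.699 s/√30, lies wholly inside ± margin. Simulated power:

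| Margin (SD) | One pair | All six pairs |
|---|---|---|
| 0.5 | about 0.70 | 0.26 |
| 0.55 | 0.80 | 0.43 |
| 0.7 | 0.96 | 0.85 |

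The hypothesis covers all interventions, so the last column applies to it.

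**4. Precision.** The unadjusted 95% CI half-width is 2.045/√30 = 0.37 SD.

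**5. In points, as an illustration only.** If comfort is scored from 0 to 100 and the SD of paired differences is 10 to 20 points, a 0.55 SD margin is 5.5 to 11 points and a half-width of 0.37 SD is 3.7 to 7.5 points. Both the SD and the scale are assumptions: the protocol names "100-point vertical visual analogue scales" only for ocular symptoms at visit 1.

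**The case against.** The strongest reply is that the sentence is a loosely worded null for a difference test. The objective, the design section and the no-intervention condition all point that way. That reading is plausible and makes the repair a matter of drafting. It does not remove the fault, since the null is still presented as the proposition under test and non-significance cannot confirm it.

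A reader might infer that a non-significant result will be reported as equivalence. The protocol does not say so: it names no test, decision rule or reporting rule. Only the weaker statement, that it could be read that way, is supported.

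A reader might also take the sample-size sentence as a claim that 30 subjects can demonstrate equivalence. It claims only that the project would be worthwhile, directly after admitting that no calculation was possible. An openly pragmatic number is not a misstatement.

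The miss rates depend on an analysis the protocol does not name. The 44% to 64% range is for one unadjusted pair. If one intervention differs by 0.3 to 0.4 SD, the chance that all six unadjusted pairs are non-significant is lower, about 37% to 18% by simulation, and it is about 70% to 48% with Bonferroni. Table 4 also collects many scores per day, so a longitudinal analysis could be more precise. These points stand.

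Test choice, multiplicity and model may properly be left to a statistical analysis plan. Whether the principal hypothesis is one of difference or of equivalence is not left open: section 1.5 fixes it.

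**Conclusion.** The point holds. The principal hypothesis is worded as equivalence without a margin, cannot be tested in that form, and does not fit the effect-seeking objective.

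The size of the risk is moderate and depends on the analysis. With 30 completers, real differences of 0.3 to 0.4 SD would often go undetected, by a single-pair test or by an omnibus test. At 0.5 SD the omnibus test misses only about one in five. An all-pairs equivalence claim would need a margin of roughly 0.7 SD to have good power. All of this rests on one score per intervention, equal SDs across pairs and full completion. Fewer completers make it worse, and repeated scores could improve it.

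This should be fixed because it governs what the trial may conclude. It does not call into question the allocation, the conduct or the number of subjects.

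**What to change.** Reword the hypothesis in section 1.5, for example: *The null hypothesis is that mean comfort does not differ between interventions at [a time point from Table 4 named in advance, such as 6 minutes after the intervention]. Pairwise within-subject differences will be reported with 95% confidence intervals. A non-significant result will not be reported as equivalence.*

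If an equivalence claim is wanted, fix a margin in comfort-scale points before the first subject is enrolled. Claim equivalence of all interventions only if the 90% confidence intervals of all six pairs lie inside that margin.

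Keep the pragmatic sample size, but state beside it the precision it gives: an unadjusted 95% half-width of about 0.37 SD of the paired difference with 30 completers, wider with fewer completers or after adjustment for multiplicity.

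The cost is a few sentences in section 1.5, handled as an amendment under section 2.5.1 if the protocol is already approved, and a more modest conclusion. No extra subjects or procedures are needed.
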